#### Functional pre-processing

2.3.2

Preprocessing will then be performed using *fMRIPrep* 23.0.2 (Esteban et al., 2018b; Esteban et al., 2018a; RRID:SCR_016216), which is based on *Nipype* 1.8.6 (Gorgolewski et al., 2011; Gorgolewski et al., 2018; RRID:SCR_002502). See Figure 3 for an overview of the workflow. A total of 2 echo-planar imaging (EPI) field maps will be available within the input BIDS structure for each participant at each Session, one for the resting state fMRI scan and one for the diffusion scan. A *B0*-nonuniformity map (or *fieldmap*) will then be estimated based on two (or more) EPI references with topup (Andersson et al., 2003; FSL 6.0.5.1:57b01774). A reference volume and its skull-stripped version will be generated using a custom methodology of *fMRIPrep*. Head-motion parameters with respect to the BOLD reference (transformation matrices, and six corresponding rotation and translation parameters) will be estimated before any spatiotemporal filtering using mcflirt (FSL6.0.5.1:57b01774, Jenkinson et al., 2002). The estimated *fieldmap* will then be aligned with rigid-registration to the target EPI b = 0 image. The field coefficients will then be mapped on to the reference EPI using the transform. BOLD runs will be slice-time corrected to 0.559 s (0.5 of slice acquisition range 0 s-1.12 s) using 3dTshift from AFNI (Cox and Hyde, 1997, RRID:SCR_005927). The BOLD reference will then be co-registered to the T1w reference using bbregister (FreeSurfer) which implements boundary-based registration (Greve and Fischl, 2009). Co-registration will be configured with six degrees of freedom. Several confounding time-series will be calculated based on the *preprocessed BOLD*: framewise displacement (FD), DVARS (Derivative of time-series Root Mean Square of the VARiance over Voxels), and three region-wise global signals. FD will be computed using two formulations following Power [absolute sum of relative motions, Power et al. (2014)] and Jenkinson [relative root mean square displacement between affines, Jenkinson et al., 2002]. FD and DVARS will be calculated for each functional run, both using their implementations in *Nipype* (following the definitions by Power et al., 2014). The three global signals will then be extracted within the CSF, the WM, and the whole-brain masks for regression and signal correction (Jenkinson and Smith, 2001).

**Figure 3 fig3:**
[figure not shown]
Visual overview of the fMRIPrep workflow. T1w: T1-weighted.

Additionally, a set of physiological regressors will be extracted to allow for component-based noise correction (*CompCor*, Behzadi et al., 2007). Principal components will be estimated after high-pass filtering the *preprocessed BOLD* time-series using a discrete cosine filter with 128 s cut-off for the two *CompCor* variants: temporal (tCompCor) and anatomical (aCompCor). tCompCor components will then be calculated from the top 2% variable voxels within the brain mask. For aCompCor, three probabilistic masks (CSF, WM, and combined CSF + WM) will be generated in anatomical space. The implementation differs from that of Behzadi et al. (2007) in that instead of eroding the masks by two pixels in BOLD space, a mask of pixels that likely contain a volume fraction of GM will be subtracted from the aCompCor masks. This mask will be obtained by dilating a GM mask extracted from the FreeSurfer’s *aseg* segmentation, and it will ensure components are not extracted from voxels containing a minimal fraction of GM. Finally, these masks will be resampled into BOLD space and binarized by thresholding at 0.99 (as in the original implementation). Components will also be calculated separately within the WM and CSF masks. For each CompCor decomposition, the *k* components with the largest singular values will be retained, such that the retained components’ time-series will be sufficient to explain 50 percent of variance across the nuisance mask (CSF, WM, combined, or temporal). The remaining components will be dropped from consideration. The head-motion estimates calculated in the correction step will also be placed within the corresponding confounds file. The confound time-series derived from head motion estimates and global signals will be expanded with the inclusion of temporal derivatives and quadratic terms for each (Satterthwaite et al., 2013).

Frames that exceeded a threshold of 0.5 mm FD or 1.5 standardized DVARS will be annotated as motion outliers. Additional nuisance time-series will be calculated using principal components analysis of the signal found within a thin band (*crown*) of voxels around the edge of the brain, as proposed by Patriat et al. (2017). The BOLD time-series will then be resampled into standard space, generating a *preprocessed BOLD run in MNI152Nlin2009cAsym space*. Automatic removal of motion artifacts using independent component analysis (ICA-AROMA, Pruim et al., 2015) will be performed on the *preprocessed BOLD in MNI space* time-series after removal of non-steady state volumes and spatial smoothing with an isotropic, Gaussian kernel of 6 mm FWHM (full-width half-maximum). Corresponding “non-aggressively” denoised runs will be produced after such smoothing. Additionally, the “aggressive” noise-regressors will be collected and placed in the corresponding confounds file. All spatial resamplings will be performed with *a single interpolation step* by composing all the pertinent transformations (i.e., head-motion transform matrices, susceptibility distortion correction when available, and co-registrations to anatomical and output spaces). Gridded (volumetric) resamplings will be performed using antsApplyTransforms (ANTs), configured with Lanczos interpolation to minimize the smoothing effects of other kernels (Lanczos, 1964). Non-gridded (surface) resamplings will be performed using mrivol2surf (FreeSurfer). Many internal operations of *fMRIPrep* use *Nilearn* 0.9.1 (Abraham et al., 2014, RRID:SCR_001362), mostly within the functional processing workflow. For more details of the pipeline, see the section corresponding to workflows in *fMRIPrep*’s documentation.

The above boilerplate text was automatically generated by fMRIPrep and minimally edited for readability. It is released under the CC0 license.

#### Resting-state functional connectivity post-processing

2.3.3

The eXtensible Connectivity Pipeline- DCAN (XCP-D) (Ciric et al., 2018; Satterthwaite et al., 2013) will be used to post-process the outputs of *fMRIPrep* version 23.0.2 (Esteban et al., 2018b, RRID:SCR_016216). See Figure 4 for a visual overview of this workflow. XCP-D was built with *Nipype* version 1.8.6 (Gorgolewski et al., 2011, RRID:SCR_002502). Native-space T1w images will be transformed to MNI152Nlin2009cAsym space at 1*mm*^3^ resolution. The six translation and rotation head motion traces will be band-stop filtered to remove signals between 0.2 and 0.3 Hz using a fourth-order notch filter, based on Fair et al. (2020). The Volterra expansion of these filtered motion parameters will then be calculated. Framewise displacement will be calculated from the filtered motion parameters using the formula from Power et al. (2014), with a head radius of 50 mm. Nuisance regressors will be selected according to the ‘aroma’ strategy. AROMA motion-labeled components (Pruim et al., 2015), mean white matter signal, and mean cerebrospinal fluid signal will be selected as nuisance regressors (Ciric et al., 2017; Satterthwaite et al., 2013). AROMA non-motion components (i.e., ones assumed to reflect signal) will be used to account for variance by known signals. Prior to denoising the BOLD data, the nuisance confounds will be orthogonalized with respect to the non-motion components. In this way, the confound regressors will be orthogonalized to produce regressors without variance explained by known signals, so that signal would not be removed from the BOLD data in the later regression. Nuisance regressors will be regressed from the BOLD data using a denoising method based on *Nilearn*’s approach. The timeseries will then be band-pass filtered using a second-order Butterworth filter, in order to retain signals between 0.01–0.08 *Hz*. The same filter will then be applied to the confounds. The resulting time-series will then be denoised using linear regression. The denoised BOLD will be smoothed using *Nilearn* with a Gaussian kernel (*FWHM* = 3.0 *mm*).

**Figure 4 fig4:**
[figure not shown]
Overview of post-processing in XCP-D. Parcellation shown for resting-state functional connectivity estimation using the 4S156 atlas. BOLD: Blood-oxygen-level dependent fMRI.

The amplitude of low-frequency fluctuation (ALFF) (Zou et al., 2008) will be computed by transforming the mean-centered, standard deviation-normalized, denoised BOLD time-series to the frequency domain. The power spectrum will be computed within the 0.01–0.08 *Hz* frequency band and the mean square root of the power spectrum will be calculated at each voxel to yield voxel-wise ALFF measures. The resulting ALFF values will then be multiplied by the standard deviation of the denoised BOLD time-series to retain the original scaling. The ALFF maps will be smoothed with Nilearn using a Gaussian kernel (*FWHM* = 3.0 *mm*). Regional homogeneity (ReHo) (Jiang and Zuo, 2016) will be computed with neighborhood voxels using *AFNI*’s *3dReHo* (Taylor and Saad, 2013).

Processed functional timeseries will be extracted from the residual BOLD signal with *Nilearn’s NiftiLabelsMasker* for the following atlases: the Schaefer Supplemented with Subcortical Structures (4S) atlas (Schaefer et al., 2018; Pauli et al., 2018; King et al., 2019; Najdenovska et al., 2018; Glasser et al., 2013) at 3 different resolutions (156, 256, 456), the Glasser atlas (Glasser et al., 2016), the Gordon atlas (Gordon et al., 2016), the Tian subcortical atlas (Tian et al., 2020), and the HCP CIFTI subcortical atlas (Glasser et al., 2013). Corresponding pair-wise functional connectivity between all regions will be computed for each atlas, which will be operationalized as the Pearson’s correlation of each parcel’s unsmoothed timeseries. In cases of partial coverage, uncovered voxels (values of all zeros or NaNs) will either be ignored (when the parcel had *>* 50.0% coverage) or will be set to zero (when the parcel had *<* 50.0% coverage). Many internal operations of *XCP-D* use *AFNI* (Cox, 1996; Cox and Hyde, 1997), *ANTS* (Avants et al., 2009), *TemplateFlow* version 24.2.0 (Ciric et al., 2022), *matplotlib* version 3.9.2 (Hunter, 2007), *Nibabel* version 5.2.1 (Brett et al., 2022), *Nilearn* version 0.10.4 (Abraham et al., 2014), *NumPy* version 2.1.1 (Harris et al., 2020), *pybids* version 0.17.1 (Yarkoni et al., 2019), and *scipy* version 1.14.1 (Virtanen et al., 2020). For more details, see the *XCP-D* website.^3^

The above methods description text for the Resting-State Functional Connectivity Post-Processing section was automatically generated by *XCP-D* and minimally edited for readability. It is released under the CC0 license.

#### Diffusion pre-processing

2.3.4

Preprocessing will be performed using *QSIPrep* 1.0.0, which is based on *Nipype* 1.9.1 (Gorgolewski et al., 2011; Gorgolewski et al., 2018; RRID:SCR_002502). See Figure 5 for a visual review of this workflow. Any images with a *b*-value less than 100 s/mm^2^ will be treated as a *b* = 0 image. DWI data will be denoised using *DiPy*’s *Patch2Self* algorithm (Garyfallidis et al., 2014; Fadnavis et al., 2020) with an automatically-defined window size. B1 field inhomogeneity will be corrected using dwibiascorrect from Mrtrix3 with the N4 algorithm (Tustison et al., 2010).

**Figure 5 fig5:**
[figure not shown]
Diffusion pre-processing overview for QSIPrep. ANTs: Advanced normalization tools, B0: *b*-value = 0, T1w: T1-weighted.

FSL (version 6.0.3:b862cdd5)’s eddy will be used for head motion correction and Eddy current correction (Andersson and Sotiropoulos, 2016). *Eddy* will be configured with a *q*-space smoothing factor of 10, a total of five iterations, and 1,000 voxels used to estimate hyperparameters. A linear first level model and a linear second-level model will be used to characterize Eddy current-related spatial distortion. *Q*-space coordinates will be forcefully assigned to shells. We will attempt to separate field offsets from subject movement. Shells are aligned post-eddy. *Eddy*’s outlier replacement will be run (Andersson et al., 2016). Data will be grouped by slice, only including values from slices determined to contain at least 250 intracerebral voxels. Groups deviating by more than four standard deviations from the prediction will have their data replaced with imputed values. Data for the field maps will be collected with reversed phase-encode blips, resulting in pairs of images with distortions going in opposite directions. Here, b = 0 reference images with reversed phase encoding directions will be used along with an equal number of b = 0 images extracted from the DWI scans. From these pairs the susceptibility-induced off-resonance field will be estimated using a method similar to that described in (Andersson et al., 2003). The field maps will ultimately be incorporated into the Eddy current and head motion correction interpolation. Final interpolation will performed using the jac method.

Several confounding time-series will be calculated based on the preprocessed DWI: FD using the implementation in *Nipype* (Power et al., 2014). The head-motion estimates calculated in the correction step will also be placed within the corresponding confounds file. Slice-wise cross correlation will also be calculated. The DWI time-series will be resampled to ACPC, generating a *preprocessed DWI run in ACPC space* with 1.6 mm isotropic voxels. A final DWI to T1w co-registration will be performed in ants Apply Transforms using the rigid transformation from ants Registration of the b = 0 reference image in ACPC space, the pre-processed T1w image, and their respective brain masks.

Many internal operations of *QSIPrep* use *Nilearn* 0.10.1 (Abraham et al., 2014) and *Dipy* 0.18.0 (Garyfallidis et al., 2014). For more details of the pipeline, see the section corresponding to workflows in *QSIPrep*’s documentation.^4^

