#### Neuroimaging data

2.2.1

MRI data will be collected by registered MRI technologists using a single American College of Radiology (ACR)-accredited Siemens 7 T MR system (MAGNETOM Terra, Siemens Healthineers, Erlangen, Germany) at the Carle-Illinois Advanced Imaging Center. Radiofrequency excitation and signal reception use a Nova Medical 8Tx/32Rx (Nova Medical, Inc., Wilmington, MA, USA) parallel transmit head coil operated in circularly polarized (CP) mode. The system undergoes daily quality assurance (QA) procedures, including echo-planar imaging (EPI) stability and ACR phantom testing using FDA-approved coils and weekly EPI stability and Siemens’ customer QA tests using the parallel transmit head coil. The imaging sequences will include several structural, functional, metabolic, and MRE sequences. A magnetization prepared 2 rapid acquisition gradient echoes (MP2RAGE) (Marques et al., 2010) will be used for the T1-weighted structural scan (further details are included in Table 2). Resting-state fMRI data will be collected using the Center for Magnetic Resonance Research (CMRR) multiband sequence (10.7 min, 1.18 s TR, 25 ms TE, 1.6 mm^3^ isotropic voxel size, multiband factor of 5, and iPAT factor of 2), (Moeller et al., 2010; Feinberg et al., 2010; Xu et al., 2013) with phase-encoding direction-flipped field maps (Auerbach et al., 2013). DWI data will also be collected with the CMRR multiband sequence (Auerbach et al., 2013; Setsompop et al., 2012) (1.6 mm^3^ isotropic voxel size, 64 directions at *b* = 1000 *s/mm*^2^ and at *b* = 2000 *s/mm*^2^, 4 *b* = 0 volumes, multiband factor of 4 with iPAT factor of 3) and accompanying phase encode reversed field maps. A T2*-weighted, high resolution gradient echo (G)RE sequence will be used for hippocampal imaging. High resolution spectroscopic mapping will use custom SPICE sequences (metabolite acquisition: 3 mm isotropic voxel size, TR 150 ms, TE 1.4 ms, flip angle 26 degree, matrix size = 78x78x24, vector size = 184; water (T1/T2/QSM/T2*) acquisition: 1 mm isotropic voxel size 55 ms TR, 1.4 ms TE, 3 T1 frames (flip angles: 7, 17, 27 degrees), 3 T2 frames (preparation times: 40, 70, 100 ms), matrix size = 224x216x72; total scan time for all acquisitions = 7 min) (Guo et al., 2019; Guo et al., 2021; Guo et al., 2025). Quantitative Susceptibility Mapping (QSM) will use A Simple Phase Imaging REconstruction method (ASPIRE; Eckstein et al., 2018) phase unwrapping. Tissue mechanical property mapping will be performed using a custom multiband spiral MRE pulse sequence as in Johnson et al. (2013, 2014) with 1.25 mm^3^ isotropic resolution, in-plane parallel imaging factor of 4, multiband excite 2 slices and encode 2 slices, 50 Hz actuation, with 4 time offsets, 78 mT/m encoding gradient. The sensitivity of the MRE sequence is 0.452 rad/*μ*m (Guenthner et al., 2018). Actuation is performed for the MRE using a Resoundant (Rochester Minnesota) and a head pad. The B1 field will be mapped using the dual refocusing echo acquisition mode (DREAM) sequence (Ehses et al., 2019; Nehrke and Börnert, 2012). MRI scan sessions are split into two same-day one-hour parts as needed with a break. When feasible to collect, a FLAIR image will be acquired at 0.7 mm isotropic voxel size, using a T2 SPACE non-selective dual-inversion recovery sequence with TI1/TI2 of 3120/450 ms.

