
**Table 2 tab2:** MRI acquisition parameters for the CUPS 7 Tesla MRI data.

Scan	TR (s)	TE (ms)	Flip angle (degrees)	Voxel size	Number of slices	Other
MP2RAGE	4.53	2.26	4 TI1, 5 TI2	0.75 mm isotropic	240	TI1/2 = 750/2950, GRAPPA acceleration factor = 3, slice partial Fourier = 6/8
Resting-state fMRI	1.18	25	60	1.6 mm isotropic	95	520 time-points
DWI	3.7	89.6	90	1.6 mm isotropic	92	64 directions, b = 1,000, 2000
T2*- weighted	1.12	20	52	0.35×0.35 ×1 mm	56	aligned perpendicular hippocampus
Spectroscopic mapping (metabolite/water)	0.150/0.055	1.4/1.4	26 3 T1 frames 7, 17, 27	3 mm isotropic/1 mm isotropic	72	vector size = 184, matrix size = 78x78x24 matrix size = 224x216x72, 3 T2 frames (TP = 40, 70, 100 ms)
QSM	46	4, 8, 12…40	9	1.0 mm isotropic	144	10 echoes
Tissue stiffness mapping (MRE)	0.160	80	-	1.25 mm isotropic	96	50 Hz encoding, flow compensated gradients, 0.452 rad/*μ*m sensitivity
FLAIR	8.0	264	120	0.7 mm isotropic	224	Non-Sel DIR TI1/2 = 3120/450
B1 DREAM	6.0	1.12, 2.19	60	4.0 mm isotropic	52	

TR, Repetition time; TE, echo time; MP2RAGE, Magnetization prepared rapid acquisition gradient echoes; TI, inversion time; GRAPPA, Generalized autocalibrating partially parallel acquisitions; fMRI, Functional magnetic resonance imaging; DWI, Diffusion-weighted imaging; TP, Time of preparation; QSM, Quantitative susceptibility mapping.

A qualified study team member or an MRI technologist may note an incidental research image observation in a scan of a CUPS participant. If the observation is made by a study team member, they would then alert the CIAIC MRI technologists. The CIAIC MRI technologists will note the randomized participant identification numbers of any studies to be reviewed. These randomized participant identification numbers will be transmitted to the physician for their review. For each participant in this list, the reviewer will review a limited set of images. The anticipated turnaround time for the physician to review and report back on the incidental research observation is about 1 week. If a completed review form has the option “YES” selected for “recommend follow-up with a primary care provider,” then the research participant liaison will be notified. The research participant liaison would then provide the imaging files to the participant and will advise them to contact their primary care physician for further consultation and evaluation. This interaction is guided by a script and cover letter.

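### Diffusion outlier replacement tests single slices although four slices are excited together, which lowers sensitivity to moderate shared dropouts and can leave one event only partly replaced

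*Protocol article*

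**What the plan says.** All references are to the protocol article. Section 2.2.1 (Neuroimaging data) specifies the diffusion acquisition with "multiband factor of 4 with iPAT factor of 3". The diffusion row of Table 2 reads "1.6 mm isotropic 92 64 directions, b = 1,000, 2000", that is, 92 slices.

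Section 2.3.4 (Diffusion pre-processing) states that eddy's outlier replacement will be run. It fixes three things:

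- the unit and the minimum size: "Data will be grouped by slice, only including values from slices determined to contain at least 250 intracerebral voxels"
- the threshold and the action: "Groups deviating by more than four standard deviations from the prediction will have their data replaced with imputed values"

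No section mentions detection by multiband group, alone or combined with slices, and none gives a reason for testing slices singly. Section 2.3.4 also calculates framewise displacement, head-motion estimates and slice-wise cross correlation. Section 2.3.11 adds diffusion quality metrics from QSIPrep. None of these is described as replacing data.

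**The concern.** The unit that is tested differs from the unit that is acquired. Four slices share each excitation, so a movement during that excitation can corrupt all four. Two things follow when each slice is judged alone. Evidence from the other three slices is not pooled, so a moderate drop present in all four may not reach the threshold in any one of them. A single event may also be split, with some of its slices imputed and the rest kept as corrupted signal.

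The preprocessed diffusion data feed the fibre orientation, GQI and NODDI reconstructions (2.3.5.1 to 2.3.5.3) and structural connectivity. The Discussion names associations with age, physical activity and states of health as aims, and the age targets in section 2.2 put 19 + 12 + 6 = 37 of 150 participants at 60 or older. If motion were more frequent in older or less healthy participants, leftover dropout would not be evenly spread over the sample. The documents give no figure for that.

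**Working it through.** The plan states no detection rate for this step, so there is no figure of its own to reproduce. The check asks how much the choice of unit matters under a simple model.

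**Inputs from the article.** Multiband factor 4 (2.2.1); 92 slices (Table 2); single-slice unit and 4-SD threshold (2.3.4). Groups per volume: 92 / 4 = 23.

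**Assumptions, not in the documents.** Errors are normal. A dropout shifts each of the four slices by the same d, in SDs of the slice-level error. The four errors have common correlation rho. All four slices meet the 250-voxel minimum.

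**Formulas.**

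- Single slice flagged: Phi(d − 4).
- Mean of four slices: its SD is sqrt((1 + 3·rho)/4), so the group is flagged with probability Phi(2d/sqrt(1 + 3·rho) − 4).
- Example, d = 3: slice Phi(−1) = 15.9%. Group at rho = 0: Phi(6 − 4) = 97.7%. Group at rho = 0.5: Phi(6/1.581 − 4) = Phi(−0.205) = 41.9%.

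| d | slice rule, each slice | group mean, rho = 0 | rho = 0.3 | rho = 0.5 |
|---|---|---|---|---|
| 2 | 2.3% | 50.0% | 13.6% | 7.1% |
| 3 | 15.9% | 97.7% | 63.8% | 41.9% |
| 4 | 50.0% | >99.9% | 96.4% | 85.5% |
| 5 | 84.1% | >99.9% | 99.9% | 99.0% |
| 6 | 97.7% | >99.9% | >99.9% | >99.9% |

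The shift at which detection is 50% is 4 SD for the slice rule. For the group mean it is 2·sqrt(1 + 3·rho): 2.00 at rho = 0, 2.76 at rho = 0.3, 3.16 at rho = 0.5, and 4.00 at rho = 1, where nothing is gained.

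**Split events under the slice rule.** With independent errors, let p = Phi(d − 4). All four slices are flagged with probability p^4 and at least one with 1 − (1 − p)^4. For rho above 0, the same quantities were integrated over a shared normal error component.

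| d | rho | at least one of four | all four | some but not all |
|---|---|---|---|---|
| 3 | 0 | 49.9% | 0.06% | 49.8% |
| 3 | 0.3 | 42.5% | 0.8% | 41.6% |
| 4 | 0 | 93.8% | 6.3% | 87.5% |
| 4 | 0.3 | 86.0% | 14.0% | 71.9% |
| 5 | 0 | 99.9% | 50.1% | 49.8% |
| 5 | 0.3 | 99.2% | 57.6% | 41.6% |

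**False flags.** One tail beyond 4 SD is 3.17 × 10^−5. The volume count depends on how section 2.2.1 is read: 2 × 64 + 4 = 132 if there are 64 directions per shell, with the four unweighted volumes from "4 *b* = 0 volumes, multiband factor of 4 with iPAT factor of 3"; 64 + 4 = 68 if there are 64 in all.

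- 132 volumes: slice tests 92 × 132 = 12,144, expected false flags 0.38; group tests 23 × 132 = 3,036, expected 0.10.
- 68 volumes: slice tests 6,256, expected 0.20; group tests 1,564, expected 0.05.

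Adding the group test to the slice test therefore adds at most about 0.10 falsely flagged groups per scan, or about 0.4 slices out of 12,144.

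**The case against.** A reader might infer that the slice rule largely misses multiband dropouts. The documents do not support that. They give no dropout size, residual SD or between-slice correlation, and shifts of 2 to 4 SD are exactly where a 4-SD rule must do poorly. A dropout in four slices gives four separate tests: at 5 to 6 SD, 84 to 98% of affected slices are flagged, and even at 4 SD at least one of the four is flagged in 86% (rho = 0.3) to 94% (rho = 0) of events. This stands, and it limits the point to moderate dropouts and to split events.

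The equal-shift model also favours the group mean. If one slice shifts by 6 SD and three do not shift, the group z at rho = 0 is (6/4)/(1/2) = 3, so the group is flagged with probability Phi(−1) = 16%, against 98% for that slice alone. This stands too, and is why the slice test must be kept and not replaced.

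A reader might further infer biased age or health associations. Greater motion with age is plausible, but the documents neither state nor quantify it, and no sample size or error rate depends on this setting. The motion estimates and quality metrics would help identify poor scans, and the release of raw data lets others reprocess. Neither repairs the study's own derived maps.

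Finally, slice-wise testing is a complete, stated choice, and the article contradicts itself nowhere on it. That is so. The point is that the chosen unit does not fit the stated acquisition and no reason is given.

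**Conclusion.** The point holds in limited form. Grouping by single slice does not match an acquisition of 23 four-slice excitations per volume. Under the assumed model this costs sensitivity to shared dropouts of roughly 2 to 4 SD per slice. At 3 SD, for example, a slice is flagged with probability 16%, against 98%, 64% or 42% for the group mean at rho = 0, 0.3 or 0.5. The gain shrinks as correlation rises and vanishes at rho = 1. Events up to about 5 SD are also often replaced only in part. Large dropouts are mostly caught already. How many dropouts are missed in this study, and whether any association is distorted as a result, cannot be derived from the documents. This is an inexpensive improvement to preprocessing and does not threaten the design.

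**What to change.** In section 2.3.4, specify that eddy's outlier replacement will use combined detection, by slice and by multiband group, at the same 4-SD threshold, with the slice grouping supplied from the acquisition. Confirm first that this grouping information reaches the pipeline and that the QSIPrep and FSL versions named in that section accept the option; the article does not say. If single-slice detection is kept, give the reason. In either case report the number of replaced slices, and of replaced groups where used, per participant, so that users can see whether replacement varies with age or health.

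No new data are needed. The cost is a small configuration change, a sentence in 2.3.4 and slightly more imputed data: the false flags estimated above, plus any genuine moderate dropouts newly caught.
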